## 8. STUDY ASSESSMENTS AND PROCEDURES

The investigator (or an appropriate delegate at the investigator site) must obtain a signed and dated ICD before performing any study specific procedures.

Study procedures and their timing are summarized in the [SoA](#). Protocol waivers or exemptions are not allowed.

Safety issues should be discussed with the sponsor immediately upon occurrence or awareness to determine whether the participant should continue or discontinue study intervention.

Adherence to the study design requirements, including those specified in the [SoA](#), is essential and required for study conduct.

All screening evaluations must be completed and reviewed to confirm that potential participants meet all eligibility criteria. The investigator will maintain a screening log to record details of all participants screened and to confirm eligibility or record reasons for screening failure, as applicable.

Procedures conducted as part of the participant's routine clinical management (eg, blood count) and obtained before signing of the ICD may be utilized for screening or baseline purposes provided the procedures met the protocol-specified criteria and were performed within the time frame defined in the [SoA](#).

Every effort should be made to ensure that protocol-required tests and procedures are completed as described. However, it is anticipated that from time to time there may be circumstances outside the control of the investigator that may make it unfeasible to perform the test. In these cases, the investigator must take all steps necessary to ensure the safety and well-being of the participant. When a protocol-required test cannot be performed, the investigator will document the reason for the missed test and any corrective and preventive actions that he or she has taken to ensure that required processes are adhered to as soon as possible. The study team must be informed of these incidents in a timely manner.

For samples being collected and shipped, detailed collection, processing, storage, and shipment instructions and contact information will be provided to the investigator site prior to initiation of the study.

During the COVID-19 pandemic, please refer to [Appendix 13 \(Section 10.13\)](#) for safety and efficacy assessments.

## **8.1. Efficacy Assessments**

### **8.1.1. Tumor Response Assessments**

Tumor assessments will include all known or suspected disease sites. Imaging will include contrast enhanced chest, abdomen and pelvis computed tomography or MRI scans; brain computed tomography or MRI scan for participants with known or suspected brain metastases; bone scan and/or bone x-rays for participants with known or suspected bone metastases. For participants with known computed tomography contrast allergy, a non contrast computed tomography of the chest with contrast enhanced abdominal and pelvic MRI can be used. The same imaging technique used to characterize each identified and reported lesion at baseline will be employed in the following tumor assessments.

Anti-tumor activity will be assessed through radiological tumor assessments conducted at baseline, during treatment as specified in the [SoA](#), whenever disease progression is suspected (eg, symptomatic deterioration), and at the time of withdrawal from treatment (if not done in the previous 6 weeks). Assessment of response will be made using RECIST version 1.1 (see [Section 10.11](#)).

All participants' files and radiologic images must be available for source verification and for potential IRC review.

For Part 2 only, images will be stored at a third party vendor and may be used for exploratory analysis outside the scope of the study.

#### **8.1.1.1. Determination of Radiographic Progression in Bone**

For CRPC participants in PART 1A, radionuclide bone scans will be performed according to the [SoA](#) to document bone metastases. The assessment of tumor response will be based on RECIST 1.1 criteria ([Section 10.11](#)).

Assessment of metastatic bone disease will be done by whole-body radionuclide bone scan. A bone scan will assess 5 regions of the skeleton, including skull, thorax, spine, pelvis, and extremities. Radiographic progression for bone disease is defined as the appearance of 1 or more metastatic lesions on bone scan. Confirmation with a second imaging modality (plain film, CT, or MRI) will be required when bone lesions are found in a single region on the bone scan. Appearance of metastatic lesions in 2 or more of the 5 regions on a bone scan will not require confirmation with a second imaging modality. PET is not an evaluable imaging modality for this study.

#### **8.1.1.2. Prostate-Specific Antigen**

For CRPC participants in Part 1A, blood tumor biomarker PSA testing will be performed according to the [SoA](#) to monitor PSA levels.

## 8.2. Safety Assessments

Planned time points for all safety assessments are provided in the [SoA](#). Unscheduled clinical laboratory measurements may be obtained at any time during the study to assess any perceived safety issues.

Safety assessments will include collection of AEs, SAEs, vital signs and physical examination, ECG (12-lead), laboratory assessments, including pregnancy tests and verification of concomitant treatments.

### 8.2.1. Physical Examinations

Participants will have a physical examination to include weight, assessment of ECOG performance status and height; height will be measured at baseline only.

A complete physical examination will include more comprehensive assessments of the cardiovascular, respiratory, GI, genitourinary (if needed), musculoskeletal and neurological systems in addition to the assessments for the brief physical exam listed below.

A brief physical examination will include, at a minimum, assessments of the skin, lungs, cardiovascular system, and abdomen.

Findings should be recorded in the source documents, and any change from baseline considered by the investigation to be clinically significant should be recorded as an AE in the CRF.

Investigators should pay special attention to clinical signs related to previous serious illnesses.

### 8.2.2. Vital Signs

Oral temperature, pulse rate, respiratory rate, BP, and SpO2 will be assessed.

BP and pulse rate measurements will be assessed in a sitting or semi-recumbent position (the same position should be maintained throughout the study) with a completely automated device. Manual techniques will be used only if an automated device is not available.

BP and pulse rate measurements should be preceded by at least 5 minutes of rest for the participant in a quiet setting without distractions (eg, television, cell phones).

Vital signs (to be taken before blood collection for laboratory tests) will consist of 1 pulse rate and 2 BP measurements (2 consecutive blood pressure readings will be recorded at intervals of at least 1 minute). The average of the 2 BP readings will be recorded on the CRF.

In addition, SpO2 should be assessed by pulse oximeter as part of the vital signs.

### 8.2.3. Electrocardiograms

Standard 12-lead ECGs utilizing limb leads (with a 10-second rhythm strip) should be collected at times specified in the [SoA](#) section of this protocol using an ECG machine that automatically calculates the heart rate and measures PR, QT, and QTcF intervals and QRS

complex. Alternative lead placement methodology using torso leads (eg, Mason-Likar) is not recommended given the potential risk of discrepancies with ECGs acquired using standard limb lead placement. All scheduled ECGs should be performed after the participant has rested quietly for at least 10 minutes in a supine position.

At each time point (see the [SoA](#)), 3 consecutive ECGs will be performed at approximately 2 minutes apart to determine the mean QTcF interval.

To ensure safety of the participants, a qualified individual at the investigator site will make comparisons to baseline measurements. Additional ECG monitoring will occur if a) the mean value from the triplicate measurements for any postdose QTcF interval is increased by  $\geq 60$  msec from the baseline **and** is  $> 450$  msec; or b) an absolute QTcF value is  $\geq 500$  msec for any scheduled ECG. If either of these conditions occurs, then a single ECG measurement must be repeated at least hourly until QTcF values from 2 successive ECGs fall below the threshold value that triggered the repeat measurement. In addition, if verified QTcF values continue to exceed the criteria above, immediate correction for reversible causes including electrolyte abnormalities, hypoxia and concomitant medications for drugs with the potential to prolong the QTcF interval should be performed.

If the QTcF interval reverts to less than the threshold criteria listed above, and in the judgment of the investigator(s) and sponsor, it is determined that the cause(s) of QTcF prolongation is something other than study intervention, treatment may be continued with regular ECG monitoring. If in that timeframe the QTcF intervals rise above the threshold values, the study intervention will be held until the QTcF interval decreases to below the threshold values. Participants will then restart the study intervention at the next lowest dose level. If the QTcF interval has still not decreased to  $< 480$  msec after 2 weeks, or if at any time a participant has a QTcF interval  $> 515$  msec or becomes symptomatic, the participant will be removed from the study. Additional triplicate ECGs may be performed as clinically indicated.

In some cases, it may be appropriate to repeat abnormal ECGs to rule out improper lead placement as contributing to the ECG abnormality. It is important that leads be placed in the same positions each time in order to achieve precise ECG recordings. If a machine-read QTcF value is prolonged, as defined above, repeat measurements may not be necessary if a qualified medical provider's interpretation determines that the QTcF values are in the acceptable range.

If a participant experiences a cardiac or neurologic AE (specifically syncope, dizziness, seizures, or stroke), an ECG (triplicate) should be obtained at the time of the event.

ECG values of potential clinical concern are listed in [Appendix 7 \(Section 10.7\)](#).

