### **7. DISCONTINUATION OF STUDY INTERVENTION AND PARTICIPANT DISCONTINUATION/WITHDRAWAL**

#### **7.1. Discontinuation of Study Intervention**

In rare instances, it may be necessary for a participant to permanently discontinue study intervention (definitive discontinuation). Reasons for definitive discontinuation of study intervention may include the following:

- Objective disease progression;
- Global deterioration of health status requiring discontinuation;
- Unacceptable toxicity;
- Pregnancy;
- Significant protocol violation;
- Lost to follow-up;
- Participant refused further treatment;
- Study terminated by sponsor;

- Death;

Note that discontinuation of study intervention does not represent withdrawal from the study. If study intervention is definitively discontinued, the participant will remain in the study to be evaluated for safety follow-up and survival (Part 2 dose expansion). See the [SoA](#) for data to be collected at the time of discontinuation of study intervention and follow-up for any further evaluations that need to be completed.

In the event of discontinuation of study intervention, it must be documented on the appropriate CRF/in the medical records whether the participant is discontinuing further receipt of study intervention or also from study procedures, posttreatment study follow-up, and/or future collection of additional information.

See [Appendix 13 \(Section 10.13.3.4\)](#) for guidance for participants with active or presumed SARS-CoV2 infection.

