### **ECG Changes**

A participant who meets the QTc criteria below based on the average of triplicate ECG readings will be discontinued from the study intervention.

- QTcF >500 msec.
- Change from baseline: QTcF >60 msec.

If a clinically significant finding is identified (including, but not limited to, changes from baseline in QTcF after enrollment), the investigator or qualified designee will determine if the participant can continue in the study and if any change in participant management is needed. This review of the ECG printed at the time of collection must be documented. Any new clinically relevant finding should be reported as an AE.

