### **8.3.1. Time Period and Frequency for Collecting AE and SAE Information**

The time period for actively eliciting and collecting AEs and SAEs (“active collection period”) for each participant begins from the time the participant provides informed consent, which is obtained before the participant’s participation in the study (ie, before undergoing any study-related procedure and/or receiving study intervention), through and including a minimum of 28 calendar days, except as indicated below, after the last administration of the study intervention.

During the long-term follow-up period in this study for survival, only SAEs will be actively elicited and collected after completion of the active collection period described above. The SAEs identified during long-term follow-up will be reported to Pfizer Safety on the CT SAE Report Form only if considered reasonably related to the study intervention.

Follow-up by the investigator continues throughout and after the active collection period and until the AE or SAE or its sequelae resolve or stabilize at a level acceptable to the investigator and Pfizer concurs with that assessment.

For participants who are screen failures, the active collection period ends when screen failure status is determined.

If the participant withdraws from the study and also withdraws consent for the collection of future information, the active collection period ends when consent is withdrawn.

If a participant definitively discontinues or temporarily discontinues study intervention because of an AE or SAE, the AE or SAE must be recorded on the CRF and the SAE reported using the CT SAE Report Form.

Investigators are not obligated to actively seek AEs or SAEs after the participant has concluded study participation. However, if the investigator learns of any SAE, including a death, at any time after a participant has completed the study, and he/she considers the event to be reasonably related to the study intervention, the investigator must promptly report the SAE to Pfizer using the CT SAE Report Form.

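### Section 8.2.3 takes some participants with QTcF prolongation out of the study where 7.1 takes them only off treatment; read literally, Part 2 survival contacts and long-term SAE elicitation end for a toxicity-selected group

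*Protocol*

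**What the plan says.** Two sections of the protocol govern marked QTcF prolongation.

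**Section 7.1, including its ECG Changes part.** The criteria are a QTcF above 500 msec or an increase above 60 msec from baseline. The consequence concerns treatment only: "A participant who meets the QTc criteria below based on the average of triplicate ECG readings will be discontinued from the study intervention". The same section separates treatment from participation: "Note that discontinuation of study intervention does not represent withdrawal from the study". After definitive discontinuation "the participant will remain in the study to be evaluated for safety follow-up and survival", with survival limited to Part 2.

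**Section 8.2.3.** This section first describes continued treatment under monitoring, or a hold followed by a lower dose: "Participants will then restart the study intervention at the next lowest dose level". It then gives three conditions for a different outcome: QTcF not below 480 msec after 2 weeks, QTcF above 515 msec at any time, or symptoms. In those cases the text reads "or becomes symptomatic, the participant will be removed from the study".

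**Section 8.3.1** adds, on adverse event collection: "Investigators are not obligated to actively seek AEs or SAEs after the participant has concluded study participation".

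**The concern.** The protocol treats stopping study drug and leaving the study as different events. Section 7.1 deals with the first and 7.2 with the second, and 7.1 requires the records to show which applies. The two sentences just before the removal sentence in 8.2.3 speak of study intervention; the removal sentence speaks of the study. A site that follows it word for word would record a study exit for a participant whom 7.1 tells it to keep.

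Adverse events are a primary endpoint in both parts, and overall survival is a secondary endpoint in Part 2. If follow-up ends because of a cardiac safety finding, those lost are selected by toxicity. Their later survival need not resemble that of the participants who remain, and a Kaplan-Meier estimate assumes that it does.

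**Working it through.** The plan gives no figure on this point, so the check compares the passages.

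**1. Do the two rules meet in the same participant?**

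| | Section 7.1 | Section 8.2.3 |
|---|---|---|
| Trigger | Triplicate-mean QTcF above 500 msec, or rise above 60 msec | QTcF above 515 msec at any time, or symptoms, or not below 480 msec after 2 weeks |
| What ends | Study intervention | Participation in the study, as worded |
| What continues | Safety follow-up; survival in Part 2 | Not stated |

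Since 515 > 500, every triplicate mean above 515 msec meets both triggers. The overlap is certain for that group. It is not complete for the others. The 515 msec value is not stated to be a triplicate mean, and the repeat readings in 8.2.3 are single ECGs, so one reading could meet 8.2.3 without meeting 7.1.

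**2. What would a literal study exit end?**

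- *Survival contacts (Part 2 only).* The synopsis and Table 3, footnote r, schedule a telephone contact about every 3 months until the end of the trial, 2 years after the last participant's first dose. A participant removed soon after starting treatment therefore has at least about 24 months of planned follow-up left, or 24 / 3 = about 8 contacts. Someone removed later has fewer.
- *Long-term SAE elicitation (Part 2).* Under 8.3.1, SAEs are still actively elicited during survival follow-up, and those considered reasonably related are reported to the sponsor's safety group. A participant who has left the study has no such period, and the sentence "Investigators are not obligated to actively seek AEs or SAEs after the participant has concluded study participation" applies.
- *Firmness of the post-treatment assessments.* On study exit, 7.2 asks for the end-of-treatment visit only where it is possible. It also does not count incomplete withdrawal procedures as deviations provided safety was preserved, so missing data might not be flagged.

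**3. What would it not clearly end?**

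- *The 28-day AE/SAE window.* Section 8.3.1 counts it from the last administration, not from study status. The early endings it lists are screen failure and withdrawal from the study with consent withdrawn for further information. Removal under a QTcF rule is not listed.
- *The 28-day visit.* The synopsis schedules it for all participants. Footnote c of Tables 1 and 3 times it from the stop of study intervention and continues follow-up of unresolved treatment-related toxicity at least every 28 days.
- *Events already under way.* Sections 8.3.1 and 8.3.3 follow them until they resolve or stabilise.

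**4. Effect on overall survival.** SAP section 5.4 censors participants last known alive at the date of last contact. Ending the contacts would therefore move censoring to about the time of removal. In an expansion cohort of about 30, one such participant is 1/30 = 3.3% of the sample. The documents give no expected number of cases, so neither the total loss nor the bias can be calculated.

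**The case against.** The strongest reply is that the removal sentence is loose wording for removal from treatment. It follows hold and restart instructions for study intervention, the example reasons for leaving the study in 7.2 name no QTc criterion, and 7.1 already keeps anyone with a mean above 500 msec in the study. That reading is plausible. But the sentence is an instruction to sites, the list in 7.2 is not exhaustive, and nothing says which section prevails.

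A second reply is that the effect is small. Survival follow-up exists only in Part 2, overall survival is secondary, and no hypothesis is tested. Baseline QTc above 470 msec is an exclusion criterion, subject to repeat readings and case review. The visible list in section 2.2.4 of Grade 3 or higher treatment-related events seen in more than one participant contains no QT event. All this stands and limits the importance of the point. Neighbouring text in 2.2.4 is blacked out, however, so rarity cannot be established from the documents.

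A reader might infer more: that active AE/SAE collection stops on the day of the ECG finding, so that arrhythmia, syncope or death in the following weeks goes unrecorded. The documents do not support that, because the 28-day window runs from the last dose. Moreover, 8.3.1 still requires prompt reporting of any SAE, including death, that the investigator learns of after study completion and considers reasonably related.

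**Conclusion.** The contradiction is real and should be corrected. For any mean QTcF above 515 msec, 7.1 keeps the participant in the study and 8.2.3, as worded, does not. Read literally, 8.2.3 puts at risk the Part 2 survival contacts and long-term SAE elicitation for a toxicity-selected group, with potentially informative censoring of overall survival. It also makes the post-treatment assessments ambiguous in both parts.

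Two stronger readings are not supported. The first is that the whole 28-day AE/SAE window is lost. The second is that the rule picks out exactly the participants with the most severe cardiac toxicity: it also reaches those who are symptomatic or who have not fallen below 480 msec after 2 weeks, and it leaves alone those between 500 and 515 msec who recover without symptoms.

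The size is 3.3% of a cohort of about 30 per case, with an unknown number of cases. The conclusion assumes that sites apply 8.2.3 as written; if they read it as removal from treatment, nothing is lost.

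**What to change.** Reconcile 8.2.3 with 7.1 by stating whether the removal sentence ends study intervention or study participation. State in 8.2.3 that the 28-day AE/SAE follow-up and, in Part 2, survival follow-up continue as 7.1 provides.

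In the same revision the sponsor should reconcile the differing QTcF thresholds, and the discontinuation in 7.1 with the hold-and-restart instructions in 8.2.3 over overlapping values. Which threshold or treatment action is right is a clinical decision; none is proposed here.

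For follow-up, the cost is a phrase or a short sentence in the next amendment. The 28-day visit and the Part 2 survival calls are already scheduled for others who stop treatment, so no new procedures are needed.

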#### **8.2.4. Clinical Safety Laboratory Assessments**

See [Appendix 2, \(Section 10.2\)](#) for the list of clinical safety laboratory tests to be performed and the [SoA](#) for the timing and frequency. All protocol required- laboratory assessments, as defined in [Appendix 2, \(Section 10.2\)](#), must be conducted in accordance with the laboratory

manual and the [SoA](#). Unscheduled clinical laboratory measurements may be obtained at any time during the study to assess any perceived safety issues.

The investigator must review the laboratory report, document this review, and record any clinically relevant changes occurring during the study in the AE section of the CRF. Clinically significant abnormal laboratory findings are those which are not associated with the underlying disease, unless judged by the investigator to be more severe than expected for the participant's condition.

All laboratory tests with values considered clinically significantly abnormal during participation in the study or within 28 after the last dose of study intervention should be repeated until the values return to normal or baseline or are no longer considered clinically significant by the investigator or medical monitor.

If such values do not return to normal/baseline within a period of time judged reasonable by the investigator, the etiology should be identified and the sponsor notified.

See [Appendix 6 \(Section 10.6\)](#) for suggested actions and follow-up assessments in the event of potential drug-induced liver injury.

